## Abstract

**Background:**

The purpose of this randomized trial is to evaluate the early removal of postoperative drains after robot-assisted minimally invasive oesophagectomy (RAMIE). Evidence is lacking about feasibility, associated pain, recovery, and morbidity.

**Methods/design:**

This is a randomized controlled multicentric trial involving 72 patients undergoing RAMIE. Patients will be allocated into two groups. The “intervention” group consists of 36 patients. In this group, abdominal and chest drains are removed 3 h after the end of surgery in the absence of contraindications. The control group consists of 36 patients with conventional chest drain management. These drains are removed during the further postoperative course according to a standard algorithm. The primary objective is to investigate whether postoperative pain measured by NRS on the second postoperative day can be significantly reduced in the intervention group. Secondary endpoints are the intensity of pain during the first week, analgesic use, number of postoperative chest X-ray and CT scans, interventions, postoperative mobilization (steps per day as measured with an activity tracker), postoperative morbidity and mortality.

**Discussion:**

Until now, there have been no trials investigating different intraoperative chest drain strategies in patients undergoing RAMIE for oesophageal cancer with regard to perioperative complications until discharge. Minimally invasive approaches combined with enhanced recovery after surgery (ERAS) protocols lower morbidity but still include the insertion of chest drains. Reduction and early removal have been proposed after pulmonary surgery but not after RAMIE. The study concept is based on our own experience and the promising current results of the RAMIE procedure. Therefore, the presented randomized controlled trial will provide statistical evidence of the effectiveness and feasibility of the “drainless” RAMIE.

**Trial registration:**

ClinicalTrials.gov NCT05553795. Registered on 23 September 2022.

## Background

In recent years, the incidence of oesophageal cancer has increased rapidly in the Western world [1, 2]. The 5-year overall survival among patients with oesophageal cancer is between 10 and 15%, rising to 40% after curative resection [3, 4]. Improvements in overall survival after curative oesophagectomy have been observed in recent years because of centralization to high-volume centres and the growing introduction of multimodal treatment strategies [5, 6]. Therefore, the up-to-date clinical standard for resectable oesophageal cancer is curative surgical resection, often preceded by neoadjuvant treatment protocols. The latest results of minimally invasive oesophagectomy have shown a major reduction in postoperative complications and pain compared with standard open resection [7–9]. Patients with fewer complications further benefit from an improved overall survival [10].

Robot-assisted minimally invasive oesophagectomy (RAMIE) represents a further technical improvement compared to the laparoscopic procedure. It offers improved three-dimensional visualization, magnification, and mechanized control that transforms the surgeon’s larger movements into precise robotic movements, facilitating the surgeon’s ability to perform complex surgical procedures [8]. RAMIE, with its reduced invasiveness, reduces postoperative pain and leads to a rapid and enhanced mobilization of patients. In addition, it results in fewer surgical site infections, less pulmonary impairment, and fewer complications. This leads to a faster recovery, shortens the length of hospital stay, and saves health care costs. There is evidence that disease-free and overall survival are not influenced by RAMIE. Regarding this background, currently, the minimally invasive approach should be favoured because of the lower postoperative morbidity [10].

A further advance in surgical care was the introduction and implementation of enhanced recovery after surgery (ERAS) programmes designed to reduce the physical and psychological stress of patients undergoing surgery, thereby accelerating postoperative recovery and reducing perioperative morbidity, hospital stay, and healthcare costs [11, 12]. Studies have shown that ERAS concepts can also be performed safely during oesophageal surgery. The data reflect that early postoperative mobilization of the patient, preferably on the day of surgery, dispensing with nasogastric tubes and drains contributes to a sustained impact on postoperative morbidity and hospital stay [13].

In recent years, chest drain management strategies have therefore undergone sustainable changes.

Chest drain management is also a crucial factor determining the postoperative course in patients undergoing RAMIE, influencing postoperative pain and the speed of functional recovery, and thereby the length of hospital stay. Two chest drains have traditionally been used to drain the right pleural cavity after oesophageal resections. One was placed at the apex to drain the air, while the second was placed at the recessus to drain the pleural effusion [14]. Interestingly, the incidences of postoperative pulmonary complications and thoracocentesis were not significantly different between early and late chest drain removal in patients after oesophagectomy with three-field lymph node dissection. Furthermore, early removal of chest drains supports early initial mobilization after surgery [15]

Given the above, we aim to investigate the potential advantages of RAMIE in oesophageal cancer without postoperative chest drains compared with the postoperative use of chest drains, which is considered the standard worldwide. The primary hypothesis is that avoidance of chest drains during the postoperative course after RAMIE can further reduce postoperative pain, improve functional recovery, and shorten hospital stay compared with the use of chest drains.

## Methods

### Aim of the study

This study aims to evaluate two different chest drain management strategies in patients undergoing RAMIE for oesophageal cancer with regard to perioperative complications until discharge. The study’s primary objective is to investigate whether the intensity of postoperative pain can be significantly reduced by avoiding chest and abdominal drains within 3 h after RAMIE, resulting in a drainless postoperative course. We assume that this will influence secondary endpoints such as early recovery and length of hospital stay.

### Trial design, study registration, and ethics

The title of this clinical trial is “Drainless Robot-assisted Minimally Invasive Oesophagectomy” (RESPECT Trial). The study is designed as a randomized controlled multicentric, two-arm parallel-group superiority surgical trial with an interventional group (A: robot-assisted minimally invasive oesophagectomy with early removal of the chest drain) and a control group (B: robot-assisted minimally invasive oesophagectomy with chest drains). The study is coordinated by the leading Study Center of the Department of Visceral, Thoracic and Vascular Surgery, Universitätsklinikum Carl Gustav Carus, Technische Universität Dresden, Germany.

Participating centres at the trial commencement are the two certified university centres: the Department of Visceral, Thoracic and Vascular Surgery, Universitätsklinikum Carl Gustav Carus, Technische Universität Dresden, Germany, and the Department of General, Visceral and Transplantation Surgery, University Hospital Heidelberg, Heidelberg, Germany. Additional centres can be evaluated for participation if equivalent standards for the operation (RAMIE procedure with equal technique) and trial management can be guaranteed at these sites. The trial was registered in advance at ClinicalTrials.gov (https://clinicaltrials.gov/ct2/show/NCT05553795). The study protocol was approved by the Ethical Committee at the Technische Universität Dresden (BO-EK-77022021). Any modifications to the protocol will require a formal amendment of the protocol. Amendments will be re-evaluated and approved by the responsible independent ethics committees. The principal investigator will notify the participating centres and send a copy of the revised protocol to the responsible investigator to add to the Investigator Site File. Furthermore, an update of the trial register will be initiated.

#### Eligibility

##### Inclusion criteria

All patients scheduled for elective RAMIE for oesophageal cancer with intrathoracic oesophagogastrostomy (Ivor-Lewis) may be included in this study. Further inclusion criteria are as follows: patients of any sex, age ≥ 18 years, American Society of Anaesthesiologists (ASA) score ≤ III, Eastern Cooperative Oncology Group (ECOG) status ≤ II, suitability for both management strategies, ability to understand the characteristics, and individual consequences of the clinical trial and written informed consent.

##### Exclusion criteria

The exclusion criteria are as follows: open oesophagectomy (either abdominal or thoracic), emergency operations, chronic pain syndromes requiring routine analgesics, simultaneous lung resection, or major lung laceration that has been sutured or stapled. Furthermore, the presence of contraindications to the use of epidural anaesthesia (e.g. coagulopathies, anticoagulation disorders, or allergies), participation in a competing interventional trial and impaired mental state will prohibit inclusion.

### Withdrawal criteria

Trial subjects may withdraw from the trial at their request or if RAMIE is not performed (e.g. due to technical irresectability, conversion to conventional resection, or metastatic disease). However, patients’ withdrawal and reasons will be described by a CONSORT flow diagram to ensure full transparency.

### Interventions

#### Surgical technique

To avoid the risk of learning-associated bias, only surgeons with sufficient proficiency will be allowed to perform the randomized interventions. Surgeons involved in the trial as the responsible surgeons must have a personal operative experience of at least 20 RAMIEs. The standard technique and surgical instruments may vary in several aspects. The technique of the Dresden Center was described elsewhere [16–18]. Guidelines for the present study are as follows:The abdominal part can be performed either laparoscopically or robotically.Intraoperative abdominal drains can be placed through the trocar sites in both groups.The patients are then placed in a left lateral decubitus position.The thoracic part is performed robotically in all cases. A circular, end-to-side, oesophagogastrostomy after gastric tube pull-up is performed over muscle-sparing mini-thoracotomy to reduce postoperative pain.Randomization is performed intraoperatively after the completion of the oesophagogastrostomy.Two 24 Charrière (Ch) chest drains are inserted through trocar sites robotic arms 1 and 3 (R1 and R3) at the end of the procedure in the control group; one 24 Ch chest drain is inserted through trocar site robotic arm 3 (R3) in the intervention group. The chest drains are immediately connected to the vacuum suction device to remove the remaining postoperative air in the right pleural cavity.Muscles at the trocar sites will be sutured with resorbable material (e.g. Vicryl 2–0 or equivalent) in a single stitch technique.Chest drains will be secured with a non-resorbable suture anchored to the skin. This should prevent excessive travel of the drain in and out of the chest wall. The suture will be looped several times around the drainage to achieve airtight wound closure after the drainage has been removed by knotting the suture. The skin incision can be closed on each side of the chest tube, usually with additional sutures if necessary. Further skin incisions will be closed with resorbable sutures (3–0 or equivalent) or staplers.The patient is turned into a supine position for extubation or transferal to the intensive care unit.In the intervention group, abdominal drains (if inserted) and chest drains (if air leak is < 100 ml/min, not increasing over 2 min, pneumothorax < 2.5 cm and no signs of active bleeding are present) are removed after chest X-ray 3 h after the end of surgery.In the control group, abdominal drains are removed after 3 h, and the two chest drains remain in place (suction − 15 mmHg). These drains are removed during further postoperative days according to a standard algorithm (see below).According to the standard algorithm, a chest X-ray is performed on POD1 and POD 3. The first chest tube can be removed at POD 3 if the daily secretion is below 450 ml per 24 h and if there is no evidence of an air leak (< 100 ml/min), pneumothorax > 2.5 cm, chyle leak, purulent secretion or bleeding followed by chest X-ray for control. On POD 6, chest drain 2 is removed if the daily secretion is below 450 ml per 24 h, followed by radiographic control. Deviations because of clinical conditions or logistic delays are allowed.

#### Perioperative pain management

The thoracic epidural catheter is placed preoperatively (before induction of anaesthesia) at the vertebral level of Th 6–9. After a test dose with 3.5 ml 1% prilocaine to exclude intraspinal placement, epidural regional anaesthesia will be started with a bolus injection of 10 ml ropivacaine hydrochloride 0.3% and 20 µg sufentanil after induction of anaesthesia and at least 20 min before skin incision. Immediately afterwards, a continuous infusion of 5 ml/h ropivacaine hydrochloride 0.2% will be maintained for at least 2 days. Additional epidural boluses of 5 ml are allowed every 20 min at the discretion of the anaesthesiologist during the operation and according to the need of the patient postoperatively. After the initial 200-ml bag of ropivacaine hydrochloride, 0.2% plus 0.5 µg/ml sufentanil is empty, the replacement will be done without sufentanil, with pure ropivacaine hydrochloride 0.2%. Postoperatively, the concomitant pain medication will consist of 1 g of metamizole or 1 g of paracetamol 4 times daily. That can be extended to 10 mg extended-release oxycodone (every 12 h) and an on-demand medication of 10 mg immediate-release oxygesic if necessary, in case of a persistent pain score > 4 according to the numeric rating scale (NRS).

The running rate and dosage will be checked daily by the pain service and adjusted to the individual needs of the patient (including increasing the basal rate to a maximum of 8 ml/h, reducing/terminating the basal rate of continuous epidural infusion and removal of the catheter).

### Assignment and randomization

All patients will be screened for eligibility considering the inclusion criteria on the day of admission (standard: the day before the surgery). Screened and eligible patients will be included in the trial after obtaining written informed consent. After obtaining written informed consent, randomization will be performed intraoperatively after completion of the oesophagogastrostomy and verification of the exclusion criteria. To achieve comparable intervention groups for known and unknown risk factors, randomization will be performed using block randomization with variable block length. Randomization lists are stratified by trial sites and will be centrally generated by nQuery by the Coordination Centre for Clinical Trials. A patient will be randomized by authorized trial personnel using the electronic REDCaP® system.

### Objectives

#### Primary endpoint

Chest drains can cause postoperative pain by irritating intercostal nerves and compromising pulmonary function independent of the surgical approach [19]. Pain impairs early mobilization. Both postoperative immobility and limited pulmonary function may further exert deleterious effects on the postoperative clinical course. Therefore, the objective is to evaluate potential short-term advantages between RAMIE without abdominal and early removal of chest drains compared with the postoperative use of chest drains. The primary hypothesis is that the early removal of chest drains after RAMIE reduces pain in the early postoperative period compared with RAMIE with drains, which is currently considered standard. Postoperative pain according to a numeric rating scale (NRS) on the second postoperative day (POD) was chosen as the primary study endpoint.

#### Secondary endpoints

The secondary endpoints reflect important treatment outcomes and thus enable a comprehensive evaluation of the surgical therapy and the postoperative course of treatment.

Perioperative complications associated with oesophagectomy are defined and recorded according to the Oesophagectomy Complications Consensus Group (ECCG) definition [20]. The secondary endpoints are pain according to NRS in the period from POD 1 to 7 (daily, Table 1), mean postoperative pain (NRS) on POD 2–4, additional (> standard) analgesic drug use during POD 2–4, drain secretion volumes, operating time, blood loss, conversion rate, number of postoperative chest X-ray and computed tomography (CT) scans, interventions including chest CT drain or chest tube replacement, postoperative mobilization (steps per day as measured with an activity tracker), and time to functional recovery. Time to functional recovery will be defined as the postoperative time point at which the following criteria are fulfilled: absence of all wound/chest drains and no requirements of intravenous analgesics and tolerance of oral intake and ability to mobilize independently.

**Table 1 Tab1:** Determination of postoperative pain during study visits

Abdominal pain?	NRS 0-10
Chest pain?	NRS 0-10
Others?	NRS 0-10
Pain on exertion?	NRS 0-10
Maximum pain since surgery?	NRS 0-10
Minimal pain since surgery?	NRS 0-10
Is your mobility or movement impaired by the pain?	Yes/no
Is the pain affecting your ability to cough or breathe deeply	Yes/no
Did the pain wake you up during the night	Yes/no
Is your mood affected by the pain?	Yes/no
Have you felt very tired since the operation?	Yes/no
Have you suffered from nausea since the operation?	Yes/no
Have you vomited since the operation?	Yes/no
Would you have liked to have more painkillers received?	Yes/no
How satisfied are you with the pain treatment you have received since the operation?	0–10°

0 = very dissatisfied; 10 = very satisfied

Furthermore, oesophagectomy-associated postoperative morbidity (pneumothorax, pleural effusion, chylothorax, pneumonia, anastomotic leakage, surgical site infection), in-hospital mortality, length of intensive care unit (ICU) stay, and hospital stay will be analysed. Postoperative morbidity from index surgery to discharge will be assessed using the comprehensive complication index based on the Clavien‒Dindo classification.

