### Trial visits

The trial includes a total of nine study visits during the operation and the postoperative period. The inclusion and exclusion criteria will be evaluated during the screening visit (the day before the operation). After the patient has given his or her informed consent, the demographic and baseline data, medical history, current medication, comorbidities, American Society of Anaesthesiologists (ASA) classification, and ECOG status will be evaluated and documented. Randomization will be performed intraoperatively by authorized study personnel, and intraoperative parameters will be collected.

Patients are followed up until discharge. Study visits will be scheduled on postoperative days 1 to 7 and on the day of discharge from the hospital. There will also be a daily visit by the pain service until the epidural catheter is removed. Primary and secondary endpoints and (serious) adverse events (SAEs and AEs) will be evaluated and documented during each visit and documented on the case report form (CRF). All planned study visits are summarized in Table 2. Data from patients without RAMIE (conversion, inoperability) will be documented until the time of the operation (visit 1). Routine blood tests (including haemoglobin concentration, leucocyte count, and serum C-reactive protein) will be performed during the postoperative visits on PODs 2, 4, and 6. In addition, postoperative chest X-rays are performed routinely on postoperative days 1, 3, and 6 independent of the study intervention or additionally according to the clinical course. According to the protocol, a CT scan of the thorax or abdomen or diagnostic endoscopy will not be routinely performed during the study period. These diagnostic examinations are only indicated based on a medical rationale (e.g. control scan of pneumothorax before or after chest drain removal, suspected fluid collection or abscess, elevated C-reactive protein or leucocyte count, suspicion of anastomotic leakage).

**Table 2 Tab2:** Study visits

Documentation	Screening day of admission	Day of operation	PODs 1–7 or until epidural catheter is removed	Day of discharge
Inclusion criteria	X			
Exclusion criteria	X	X		
Patient characteristics	X			
Randomization		X		
Surgical technique		X		
NRS pain scale			X	
Morbidity			X	X

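### Time to functional recovery requires all drains to be out, and drain timing is set by arm, so this secondary endpoint can show a benefit when recovery is identical

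*Protocol article*

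**What the plan says.** In the protocol article, Secondary endpoints, the definition begins: "Time to functional recovery will be defined as the postoperative time point at which the following criteria are fulfilled: absence of all wound/chest drains". Four criteria must hold together: "absence of all wound/chest drains and no requirements of intravenous analgesics and tolerance of oral intake and ability to mobilize independently". No version without the drain criterion is given.

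The Surgical technique section sets drain removal by arm:

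- **Intervention.** One chest drain, removed 3 h after the end of surgery if the air-leak, pneumothorax and bleeding conditions are met.
- **Control.** Two chest drains stay in. For the first, "The first chest tube can be removed at POD 3 if the daily secretion is below 450 ml per 24 h", with further conditions. For the last, "On POD 6, chest drain 2 is removed if the daily secretion is below 450 ml per 24 h".
- **Both arms.** Abdominal drains, where placed, are due out at 3 h, so only the chest drains separate the arms. Departures for clinical or logistic reasons are permitted.

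The Background puts recovery into the hypothesis: avoiding drains "can further reduce postoperative pain, improve functional recovery, and shorten hospital stay compared with the use of chest drains". The section on the primary endpoint states the primary hypothesis as pain alone. The Statistics section lists several methods for secondary endpoints, Kaplan-Meier among them, to be used as appropriate.

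**The concern.** One of the four criteria is largely the randomised treatment itself. Take two patients who both eat, walk independently and need no intravenous analgesia on POD 4. The one in the intervention arm, with the drain out on schedule, is recorded as recovered on POD 4. The one in the control arm, also on schedule, is recorded on POD 6. The two-day difference comes from the drain timetable and not from how the patients are doing.

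The endpoint bears the name of something the trial hopes to improve. If a between-arm difference in it were read as faster functional recovery, part or all of that difference could be the schedule. Analysis cannot repair this afterwards if only the composite is compared, because the drain criterion sits inside the definition.

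**Working it through.** **The plan's own figure.** The article gives no figure for time to functional recovery. Its sample size, for POD 2 pain, reproduces. With a difference of 1 point, SD 1.4 and two-sided 5%, the noncentral t gives power 0.790 at 31 per group and 0.803 at 32. Then 32 / 0.9 = 35.6, so 36 per group and 72 in total. Nothing below changes this.

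**Definition as a formula.** Let R be the day on which the three other criteria are all met, and D the day on which the last drain is out. The endpoint is max(R, D).

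- Intervention on schedule: D is about 3 h, or 0.125 day, so the endpoint equals R.
- Control on schedule: D = 6, so the endpoint equals max(R, 6).
- With the same distribution of R in both arms, the mean difference is the mean of max(R, 6) − R. This is zero only if nobody meets the other criteria before POD 6.

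**Inputs from the article:** the four criteria, removal at 3 h and on POD 6, 36 per arm, two-sided 5%.

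**Assumptions, not in the article:** R is lognormal, identical in both arms and rounded up to whole days. The median and log-SD of R are varied. The log-rank test is used for illustration, since the article names no specific test for this endpoint.

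**Results with drains on schedule.** The table shows the share of trials with a significant log-rank test although recovery is identical.

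| Median of R | 36 per arm, log-SD 0.35 | 32 per arm, log-SD 0.4 | Mean difference (second setting) |
|---|---|---|---|
| POD 4 | about 100% | 97.5% | 1.5 days |
| POD 5 | about 50% | 45% | 0.9 days |
| POD 6 | 11% | 11% | 0.5 days |
| POD 7 | 4% | 4% | 0.3 days |

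At a median of POD 4 the recorded medians are about 4.5 versus 6.0 days; the 4.5 reflects rounding up to whole days. The Mann-Whitney test is more affected: in the second setting it gives 70% at POD 5 and 20% at POD 6.

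**Results with drains off schedule.** Suppose 20% of intervention drains stay to POD 6 and 30% of control drains come out on POD 3 to 5. With 36 per arm the log-rank figures become about 68%, 18%, 6% and 5% at medians of POD 4, 5, 6 and 7.

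**Results without the drain criterion.** Comparing R alone, with 32 per arm, the log-rank test rejects in about 3 to 6% of trials in every scenario, in line with the nominal 5%.

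**The case against.** The case on the other side has substance.

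- **It is one secondary endpoint among many.** The only confirmatory analysis is pain on POD 2. Steps per day, additional analgesic use, ICU stay and hospital stay also bear on recovery, and none has the drain criterion in its definition. This stands, and it limits the weight of the point.
- **The schedule is not absolute.** Removal at 3 h is conditional and deviations are allowed. This also stands. It is wrong to say that no control patient can reach the endpoint before POD 6; that holds only for one managed to the algorithm. Deviations of the kind assumed above shrink the artefact without removing it when recovery is early.
- **Being free of drains matters to patients, and the criterion can register harm.** A patient whose drain is reinserted would not count as recovered under the composite. This is a good reason to keep reporting the composite, but not to rest the claim of better recovery on it.

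A reader might go further and infer that any significant result would merely restate the allocation. The document does not support that, because it depends on most patients recovering clearly before POD 6, and the article gives no such timing.

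A reader might also count drain secretion volume and the number of chest X-rays as defects of the same kind. They do not stand as errors. No between-arm test is specified for drain volume, and descriptive handling of it belongs to an analysis plan. Protocol films come to about 4 in the intervention arm and 4 to 5 in control, which is no material imbalance. The film days under Surgical technique and under Trial visits are compatible.

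**Conclusion.** The concern holds in a limited form. Following the protocol exactly, time to functional recovery can favour the intervention when recovery on the other three criteria is identical. That follows from the definition and the drain schedule alone.

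How much it matters is not known from the document. Under the assumptions above, false significance ranges from near certain at a median of POD 4, through about one trial in two at POD 5, to nominal from about POD 7. It is lower where drains depart from schedule. These figures rest on an assumed lognormal distribution in whole days and on a log-rank test. They show a range and do not forecast this trial.

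The primary endpoint, its test and the 72 patients are untouched. This is a cheap improvement to one secondary endpoint and no threat to the main conclusion.

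**What to change.** Base the between-arm comparison, and any statement that functional recovery improved, on the three criteria not set by allocation: no intravenous analgesics, oral intake tolerated, and independent mobilisation. Record the date on which each is met. The article's data-collection section and visit table do not list these dates, so check that the case report form captures them.

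Report the four-criterion composite and time to drain-free status alongside, as descriptive measures. Keep drain reinsertion as its own endpoint so that harm from early removal stays visible. No change to drain management is implied.

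The cost is a change of wording in the endpoint definition and, if needed, a few date fields. The sample size does not change. The downside is that the reported difference may be less favourable to the intervention.

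### The analgesic component of time to functional recovery leaves out the epidural, so a patient who meets the other components can be scored as recovered while the epidural still runs

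*Protocol article*

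**What the plan says.** The Secondary endpoints section gives the definition in full. Recovery is dated to the point at which four conditions hold together: "absence of all wound/chest drains and no requirements of intravenous analgesics and tolerance of oral intake and ability to mobilize independently". Neither epidural infusion nor catheter removal appears there, and no other section adds them.

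The epidural is planned for every patient. Under Perioperative pain management, "The thoracic epidural catheter is placed preoperatively (before induction of anaesthesia) at the vertebral level of Th 6–9", and after the opening bolus "a continuous infusion of 5 ml/h ropivacaine hydrochloride 0.2% will be maintained for at least 2 days". Under Exclusion criteria, "the presence of contraindications to the use of epidural anaesthesia" bars a patient from the trial. Boluses on the patient's need are allowed after surgery, and the pain service may raise, lower or end the infusion. No upper limit on its duration is stated.

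Alongside it, "the concomitant pain medication will consist of 1 g of metamizole or 1 g of paracetamol 4 times daily"; the route is not given. Extended-release and immediate-release oral-type opioid can be added for persistent pain. No drug in the section is described as intravenous.

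On drains, the Surgical technique section says that those in the intervention arm "are removed after chest X-ray 3 h after the end of surgery", provided that set conditions on air leak, pneumothorax and bleeding are met. In the control arm the second chest drain is scheduled to come out on POD 6, subject to an output threshold, and deviations are permitted.

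**The concern.** An analgesic criterion in a recovery endpoint is meant to show that the patient no longer depends on hospital-delivered pain relief. Here it tests a route that the pain-management section never names and passes over the one on which that section is built. A patient with a running epidural, even one receiving extra boluses, is not on an intravenous analgesic and so passes.

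Two features of the trial make this worth correcting. The Background and Discussion both name better functional recovery among the benefits that drain avoidance is expected to bring, so readers will look at this endpoint. The arms also differ in when the remaining components can be met, so a lenient analgesic criterion need not affect them equally, and any difference would tend to favour the hypothesis.

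**Working it through.** The plan gives no figure for this endpoint, so there is none to reproduce. The check sets the definition against the analgesia and drain schedules.

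**Notation.** For one patient, let D be the time when the last drain is out, I the time when intravenous analgesics are no longer needed, O the time when oral intake is tolerated, M the time of independent mobilization, and E the end of epidural analgesia. If each state persists once reached:

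- present definition: T = max(D, I, O, M)
- with the epidural included: T′ = max(D, I, O, M, E)
- shift for that patient: T′ − T = max(0, E − T)

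The gap matters for a patient only if all four present components are met before the epidural ends.

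**Schedules side by side.**

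| | Intervention | Control |
|---|---|---|
| D (Surgical technique) | 3 h after surgery if conditions are met | POD 6 for the second chest drain if the output threshold is met |
| E (Perioperative pain management) | at least 2 days, no stated maximum | the same |
| I, O, M | no distribution given | no distribution given |

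**Intervention arm.** D can fall well before E, so T can precede E whenever I, O and M do. None of these three excludes a running epidural.

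**Control arm.** T is normally no earlier than POD 6. The shift is above zero only if the epidural outlasts the drains, or if drains come out early under the permitted deviations.

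**What can be bounded.** Take a patient whose epidural stops exactly at the 2-day minimum. If the 2 days count from the end of surgery, the largest conceivable shift is 48 h − 3 h = 45 h. If they count from the start of the infusion, before incision, it is less. The smallest shift is 0. Reaching 45 h would require eating, walking independently and needing no intravenous drug 3 h after oesophagectomy, so it is a ceiling and not an estimate. For longer epidurals the article sets no ceiling.

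**What cannot be computed.** The effect on the comparison is the mean of max(0, E − T) in the intervention arm minus the same mean in the control arm. That needs the joint distribution of E, I, O and M, and the article gives none of it. Nor does it give the route of metamizole or paracetamol, on which I depends.

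**Sample size.** It rests on NRS pain on POD 2 (difference 1, SD 1.4). The two-sided t-test has power 0.790 at 31 per group and 0.803 at 32, which confirms the stated 32; 32/0.9 = 35.6, rounded up to 36 per group and 72 in total. None of this involves the recovery endpoint.

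**The case against.** Five points can be made on the other side.

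1. *Four components apply, not one.* A reader might infer that stopping intravenous drugs is enough to be scored as recovered. It is not: drains, oral intake and mobilization must also be satisfied. This stands, and it limits how often the gap bites. It does not close the gap.

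2. *The intravenous criterion may still bind.* A reader might infer that it is empty in this trial. The documents do not establish that. Metamizole or paracetamol is given four times daily without a stated route. If it is intravenous in the first days (an assumption), the criterion delays recovery while the epidural runs and the gap shrinks. This stands.

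3. *The imbalance comes from the drains.* The epidural regimen is the same in both arms, and the asymmetry arises only because drain removal is set by allocation. This also stands. The drain component probably contributes more to any difference between arms than the epidural gap does.

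4. *A scheduled infusion is not the same as a need for analgesia.* Counting the epidural ties the endpoint partly to a protocol-set duration and to a pain-service decision in an unblinded trial. This is a real cost and has to be disclosed. It applies to both arms alike, which the present gap need not do.

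5. *It is a definitional choice in one secondary endpoint.* In part it is. But the definition is given in full and names one analgesic route while the regimen relies on another, so how the epidural counts should be settled explicitly.

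**Conclusion.** The point holds as a gap in a stated definition: as written, the rule can score a patient on a running epidural as recovered. This rests on the text alone. That the gap can act mainly in the intervention arm follows from the drain schedules, provided that they are broadly followed.

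A reader might go further and infer that recovery in the intervention arm is dated some days too early, or that the gap explains a material share of any difference between arms. The documents support neither. They do not show how many patients would meet the other components before the epidural ends. If oral intake or mobilization is usually reached only when the epidural stops or later, the effect is zero.

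The consequence is confined to time to functional recovery. The confirmatory test of pain on POD 2, its significance level and the sample size are untouched. This is a cheap improvement to one secondary endpoint.

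**What to change.** Change the analgesic component to *no requirement for intravenous or epidural analgesics*, and state that a running epidural infusion counts as such a requirement. Record the epidural stop time in the eCRF. The follow-up is already in place: "There will also be a daily visit by the pain service until the epidural catheter is removed" (Trial visits). Leave the analgesic regimen and the catheter-removal rules as they are; only the outcome definition changes.

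The cost is one phrase in the definition, one eCRF field and one derivation rule. Recovery times will become longer. Because the infusion is scheduled for at least 2 days in both arms, few patients can then be scored as recovered before about day 2. The report should disclose this floor. A sensitivity analysis with the present definition can be reported beside the main result, so that readers see how much the epidural criterion matters.
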